## Abstract

**Background:**

Breech presentation occurs in 3 to 4% of all term pregnancies. External cephalic version (ECV) is proven effective to prevent vaginal breech deliveries and therefore it is recommended by clinical guidelines of the Royal Dutch Organisation for Midwives (KNOV) and the Dutch Society for Obstetrics and Gynaecology (NVOG). Implementation of ECV does not exceed 50 to 60% and probably less.

We aim to improve the implementation of ECV to decrease maternal and neonatal morbidity and mortality due to breech presentations. This will be done by defining barriers and facilitators of implementation of ECV in the Netherlands. An innovative implementation strategy will be developed based on improved patient counselling and thorough instructions of health care providers for counselling.

**Method/design:**

The ultimate purpose of this implementation study is to improve counselling of pregnant women and information of clinicians to realize a better implementation of ECV.

The first phase of the project is to detect the barriers and facilitators of ECV. The next step is to develop an implementation strategy to inform and counsel pregnant women with a breech presentation, and to inform and educate care providers. In the third phase, the effectiveness of the developed implementation strategy will be evaluated in a randomised trial. The study population is a random selection of midwives and gynaecologists from 60 to 100 hospitals and practices. Primary endpoints are number of counselled women. Secondary endpoints are process indicators, the amount of fetes in cephalic presentation at birth, complications due to ECV, the number of caesarean sections and perinatal condition of mother and child. Cost effectiveness of the implementation strategy will be measured.

**Discussion:**

This study will provide evidence for the cost effectiveness of a structural implementation of external cephalic versions to reduce the number of breech presentations at term.

**Trial Registration:**

Dutch Trial Register (NTR): 1878

## Background

Breech presentation occurs in 3 to 4% of all term pregnancies [1]. In pregnancies complicated by breech presentation, perinatal mortality, neonatal mortality or serious neonatal morbidity are increased as compared to pregnancies where the fetes is in cephalic position [2]. Breech position at term occurs in 8.000 pregnancies in the Netherlands each year. Until 2000 the mode of breech delivery was controversial. Since publication of the results of the term breech trial, the caesarean delivery rate in women with a fetes in breech presentation in the Netherlands has increased from 45% to around 80% [3]. Although an elective caesarean section is safer for the baby, it increases maternal morbidity [4]. Moreover, the uterine scar carries a risk for future pregnancies [5]. External cephalic version (ECV) reduces the rate of non-cephalic presentations at term with 40-50%, and thus the number of caesarean deliveries performed for at term breech presentation, without any increased risk to the baby [6]. The high caesarean delivery rate for breech presentation makes ECV an important obstetric intervention and it is therefore recommended by the Royal College of Obstetricians and Gynaecologists in the Clinical Green Top Guidelines.

A recent inventory among Dutch gynaecologists showed that 5% of the practices never offered ECV, whereas one practice offered ECV only to multipara. In 28% of the practices an ECV was performed by all gynaecologists, whereas in the other 72% ECV was performed by a smaller team of specialists. The palette of relative contraindications differed widely, and only 19% of the responding clinics registered their success rates. The number of patients refusing ECV was estimated to be 20 to 30%. At present, 60 to 70% of the women with a fetes in breech position undergoes ECV in the Netherlands. This rate is probably an overestimation, as they are based on self reported rates by midwives and gynaecologists, in the absence of registrations. The true number of women that undergoes ECV for term breech is probably below 50%.

With 6.000 term breech deliveries each year, of which 5.000 are delivered by caesarean section, there is clearly room for improvement. The number of caesarean sections for breech delivery can de reduced with approximately 2.000 per year. As the additional costs of a caesarean section as compared to vaginal delivery are estimated to be 1.500 Euros, the potential saving of a better implementation of ECV can reduce costs with 2 to 3 million Euros per year for direct medical costs only. As pregnant women with a previous caesarean section are at increased risk of complications, and therefore always deliver under responsibility of a gynaecologist, the potential savings are even higher.

In the Netherlands, there is professional consensus among the Dutch Society for Obstetrics and Gynaecology (NVOG) as well as the Royal Dutch Organisation for Midwives (KNOV) that ECV should be offered to all women with a fetes in breech presentation at term. The KNOV has produced a leaflet for patients in which ECV is recommended. Nevertheless, the number of women potential suitable for ECV who were not offered an attempt range from 4% to 33% [7-9]. Moreover, a substantial number of women refuse ECV, and opt immediately for a caesarean section. In Australia, Raynes-Greenow and others investigated pregnant women's preferences and knowledge of term breech management [10]. 39% would choose ECV, 39% would not choose ECV, and the remaining 22% were uncertain. Yogev and colleagues performed a similar study in Israel [11]. They reported that in 1995, more than half the women (52.7%) had heard of ECV and 53.8% were willing to consider it, whereas in 2001, 73.2% had heard of it but only 23.9% were willing to consider it. Johanson reported that out of a group of 323 pregnant women with a fetes in breech presentation, 65% opted for external cephalic version after they were informed [12]. They also demonstrated an association between the gynaecologists who provided information and the level of uptake by the women.

The number of women with a breech presentation considering ECV and their knowledge about the procedure are unknown in the Netherlands. Until publication of the new NVOG and KNOV guidelines in 2001 and 2002, ECV used to be a controversial intervention. Since the introduction of these guidelines, there is no evidence for a raise in the number of ECVs performed. However, the number of birth in breech presentation at term is stable since 2002, indicating a low implementation grade of ECV.

Implementation requires a clear and deliverable evidence based message [13]. However, there are often major discrepancies between best evidence and practice, resulting in a large variation between professionals [14-17]. Based on this national and international literature, two main barriers for ECV implementation are identified 1) lack of patients' knowledge about risk for and consequences of ECV and breech delivery 2) the attitude and knowledge of midwives and gynaecologists towards ECV.

This study will show us if an implementation strategy, tailored on main barriers combining both patient and health care provider interventions, is more cost-effective than usual care. We will also evaluate the process of implementation to ascertain which elements of the strategy can be particularly associated with successful implementation of ECV. Moreover, our proposal is a collaborative effort of midwives and gynaecologists, and is supported by both the KNOV and NVOG.

## Methods/Design

### Aims

The main objective of this study is to assess barriers and facilitators of implementation of ECV in the Netherlands. We would like to create a broad social basis and awareness for the need of cooperation in care for women with a fetes in breech position. An innovative implementation strategy will be developed based on improved patient counselling and thorough instructions of health care providers for counselling.

Research questions are: What are barriers and facilitators of implementation of ECV in the Netherlands? What are the costs and effects of an innovative implementation strategy based on improved patient counselling and information of health care providers to implement the guidelines on ECV for breech presentation? What is the feasibility of this implementation strategy?

### Methods

The proposal will contain three phases. In the first phase, we will identify facilitators and barriers of implementation of ECV and create awareness of the need for improvement. Subsequently, we will develop an implementation strategy targeted on patient counselling and information of health care providers, and evaluate the cost-effectiveness of the developed strategy.

### Identification of facilitators and barriers of implementation of ECV

A topic list will be defined by an expert panel. The topic list will be constructed on the basis of existing knowledge and theories on implementation factors, primarily based on the clinical guidelines by the NVOG and KNOV. This list will be used to guide and direct semi-structured interviews and focus groups, patients, gynaecologists and midwives will be asked for their attitude towards ECV. We will assess fear for complications, skills and attitudes. A framework approach will be used to analyse the data and to derive potential factors that might influence the implementation of ECV [18].

In the second step the exploratory findings will be used to develop a series of questionnaires. These will then be distributed among a much larger number of actors. Quantitative analyses will be conducted, accounting for the multilevel nature of the problem and the corresponding data-collection, to study the prevalence of factors that facilitate and/or inhibit the implementation of external cephalic version in the Netherlands. In this process, we will take into account regional and socio-economic differences. To identify and explore relevant factors, semi-structured interviews will be held with pregnant women with a fetes in breech presentation (N = 20), general practitioners (N = 20), midwives (N = 20), gynaecologists (N = 20), and representatives of health care insurers. Respondents will be 'purposively' selected [19]. Gynaecologists and midwives will be selected on relevant characteristics of their practices (region, hospital). Moreover, we will interview partners of pregnant women separately, but also as a couple. The interviews will be guided by the topic list that is defined on the basis of existing knowledge and theories on implementation [20]. The topic list will be used to direct the interviews, but will be informally and flexible applied in order to prevent us from imposing our preconceptions. The topic list will contain themes that include knowledge of the complications of ECV, about the risks of caesarean section in terms of short- and long term maternal and neonatal mortality and morbidity, and about available evidence. We will ask couples about their attitude towards the problem, about their expectations and previous experiences, and about their beliefs about health care in general. Midwives and gynaecologists will be interviewed on similar subjects, but they will be asked more extensively about the potential effectiveness of ECV (relative risks, numbers needed to treat, numbers needed to harm) as well as the influence of wider societal, organisational, financial, and contextual factors. We expect the following categories of factors to play a role: socio-political factors (opinion stated by opinion leaders, comments in journals, opinion of experts within the own department, attitude of the head of the department), organizational factors, and knowledge and beliefs (doctor and patient level, (the lack of) knowledge, about complications of vaginal breech delivery and caesarean section, anxiety for ECV and the demand for caesarean section (patient level only)). The semi-structured interviews will be analyzed on the basis of a framework approach [18]. The analyses will help us identify the important factors that are most likely to play a role in the implementation of ECV. We expect that we will be able to distil a list of approximately fifteen issues that are of potential importance. The exploratory findings will be used to develop a questionnaire, which is supposed to be extensive and complete. The questionnaire will be sent to all midwives practices and to the departments of obstetrics and gynaecology of all hospitals in the Netherlands. Moreover, all health insures will be targeted.

Ethical approval is not needed in accordance to the prescriptions of the medical ethical committee of the AMC, if individual patients will be approached for semi structured interviews, without provocation of emotional arousal and with anonymous processing of the data study.

### Development of an implementation plan

After analysis, the results will be discussed in a final meeting with the study group and representative participants (clients, midwives, gynaecologists). Based on the discussion of these results, an implementation plan, with different actions and interventions, will be developed. Although parts of the plan will highly depend on the obstacles of change to be identified (e.g. knowledge, attitude, behaviour, logistics), we anticipate the following ingredients: 1) an educational brochure/website with evidence, one designed for gynaecologists/midwives and one designed for patients. 2) group/unit meetings to discuss the protocol, the resistance to it, and how to overcome problems in adaptation. 3) if necessary, a training in counselling patients on ECV for midwifes and/or gynaecologists can be developed 4) reminders; regular self monitoring; regular observation by heads of units. This plan will be developed according to phase 2 to 5 of Grols 5-step implementation model. Depending on the results of the proposed project, additional funding will be sought for these phases.

### Evaluation of the developed implementation strategies design

A cluster randomised controlled trial with an economic evaluation will be performed alongside. Ethical approval will be requested before the start of this part of the study. Information on counselling of patients, required for ethical approval, will be specified in the first phase of the trial. A set of quality indicators will be extracted from the NVOG and KNOV guidelines. The indicator development will be performed according to the RAND-modified Delphi method [21]. First of all, key recommendations from the guidelines will be extracted by two or three experts, the project leaders. Subsequently, the clinical relevance of all key recommendations for patient's health benefit and efficacy will be tested in two rounds among an independent panel of 12-15 experts (KNOV and NVOG guideline writers, KNOV and NVOG members, quality of care experts and patients). The key recommendations with the highest scores will be selected and made ready for use, in measurable elements (process indicators). Moreover, measurement instruments will be developed and the participating hospitals will be informed about the study. A detailed protocol on the randomised controlled trial will be written after finishing the first phase.

This is a requirement to receive further funding of the further project. This protocol is in development; it depends mainly in the outcome of the first phase. This will be followed by a pilot, feasibility study where two different implementation strategies will be tested in four participating hospitals, one primary care centre specialised in ECV and one independent midwifery practice. Before the pilot study starts, baseline characteristics and primary and secondary outcomes will be measured with questionnaires and data gathering on amount of version attempts, outcomes after ECV and caesarean section rate. The data gathering lists and questionnaires will also be developed during the first phase.

After the pilot study a cluster randomised controlled trial will be performed in which two implementation strategies will be evaluated: a patient centred strategy and a health care provider (midwife and gynaecologist) centred strategy. In the randomised clinical trial, we will allocate centres and their regions at random to four groups: A. Patient centred strategy alone, B. Healthcare providers-centred strategy alone, C. Both the patient and healthcare provider centred strategies, D. No specific implementation intervention.

Up to 30% of eligible patients are not offered an ECV attempt and up to 40% of counselled patients do not choose for ECV, which might be the result of insufficient information. With the decision aid we intend to increase the number of well informed patients from 50 to 80%. To correct for the degree of similarity among responses within a cluster, a intra-cluster correlation coefficient of 0.10 was integrated in the power analyses. To be able to show the difference of 30% with a power of 80% and an alpha error of 5%, we need 20 clusters of a 30 patients each. The gynaecologists in the participating hospitals will give informed consent for this trial to confirm that they will treat their patients conform one of the four strategies were they will be allocated to, as long as the trial is open for inclusion.

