### Implementation study

An effect and process evaluation will be performed. An effect evaluation of the two strategies will be carried out using the primary and secondary outcome measures and the set of process indicators derived from the NVOG and KNOV guidelines. This will be done among pregnant women with breech presentation at term and professionals involved in the care for these women. The measurements will be performed in the 20 participating hospitals before and after implementation of the different strategies by a medical record search, added with questionnaires among professionals and patients. The medical records will be searched using standardised registration forms. A process evaluation will be performed to study the feasibility of the two strategies. The extent by which clinicians, midwives and patients used these elements will be measured.

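### The stated 80% power is a normal-approximation figure for one arm against one arm with 5 clusters each; with cluster-level degrees of freedom that comparison has about 71–78%

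*Protocol article*

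**What the plan says.** In the section on evaluation of the developed implementation strategies, the protocol article will "allocate centres and their regions at random to four groups": patient strategy, provider strategy, both, or neither. The sample size rests on the aim to "increase the number of well informed patients from 50 to 80" per cent. It allows for clustering: "a intra-cluster correlation coefficient of 0.10 was integrated in the power analyses". The conclusion is that, "with a power of 80% and an alpha error of 5%, we need 20 clusters of a 30 patients each".

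In the Implementation study section the number of clusters reappears as a trial total: "The measurements will be performed in the 20 participating hospitals".

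The article does not say which arms or which contrast the 80% refers to, whether the test is one- or two-sided, or what the allocation ratio is.

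**The concern.** Twenty clusters over four groups is 5 per group if allocation is equal. A design-effect calculation inflates the variance for clustering, but it still treats that variance as known and uses the normal critical value. With 5 randomised clusters per arm the between-cluster variance is estimated from very few units, so the difference matters.

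At stake is whether 80% power and 5% alpha hold together for the comparison that was calculated. If they do not, a real 30-point difference between two arms is more likely to be missed than the plan says, or the 5% error rate is exceeded. The article also says that a detailed trial protocol will be written after the first phase, so the cluster number and its justification may be carried forward unchanged.

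**Working it through.** **Inputs from the article:** rates 0.50 and 0.80; intra-cluster correlation 0.10; 30 patients per cluster; 20 clusters in total; four arms; alpha 0.05; power 0.80.

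**Assumed, because not stated:** two-sided test, equal allocation, equal cluster sizes.

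**1. Reproduce the stated figure.**
- Patients per arm without clustering (pooled null variance): n = [1.96·√(2·0.65·0.35) + 0.8416·√(0.25 + 0.16)]² / 0.30² = 38.48.
- Design effect: 1 + (30 − 1)·0.10 = 3.9.
- Patients per arm: 38.48 × 3.9 = 150.07, or 150.07 / 30 = 5.00 clusters.
- Four arms × 5 clusters = 20 clusters.
- Normal-approximation power at exactly 5 against 5 clusters: 79.98%.

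Other versions of the pairwise formula give 4.65 clusters per arm (unpooled variance, 82.8% power at 5 clusters), 5.85 (continuity correction) and 4.03 (one-sided). A contrast of 10 against 10 clusters gives 98%, so it is not the source of the 80%.

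**2. Allow for the number of clusters.**
- Standard error of the difference: √(0.41 × 3.9 / 150) = 0.1032.
- Noncentrality: 0.30 / 0.1032 = 2.906.
- Degrees of freedom: 5 + 5 − 2 = 8 using the two arms compared, or 20 − 4 = 16 with a variance pooled over all four.

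| Analysis, 5 v 5 clusters | Critical value | Power |
|---|---|---|
| Normal, pooled null variance (matches the article) | 1.96 | 80.0% |
| Normal, unpooled variance | 1.96 | 82.8% |
| Noncentral t, 16 df | 2.12 | 77.9% |
| Noncentral t, 8 df | 2.31 | 72.1% |
| Beta-binomial simulation of a cluster-level t-test, 8 df | 2.31 | 70.7% |

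The t rows use the unpooled variance. With the pooled null variance they become 73.6% (16 df) and 67.7% (8 df). Simulation with 16 df gives 74% to 80%, depending on the rates assumed in the other two arms.

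**3. What if 1.96 is kept?** The two-sided tail area of t with 8 df beyond 1.96 is 8.6%; simulation of the cluster-level test gives about 8.5%. So 80% power and 5% alpha are not both met by the two-arm cluster-level test.

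**4. Main effects of the 2×2 layout, 10 against 10 clusters.**
- Standard error: √(0.41 × 3.9 / 300) = 0.0730; noncentrality 0.30 / 0.0730 = 4.109.
- Noncentral t with 18 df: 97.3% at 5%, 94.2% at 2.5%. With 16 df: 97.1% and 93.7%.
- Simulation: 96.4% and 92.9%.

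**The case against.** **The arithmetic reproduces.** This is true: the article applies the standard design-effect formula correctly. The point is that this formula is too optimistic with 5 clusters per arm, not that a sum is wrong. It is also fair that the 80.0% and the 72–78% use different variance formulas. Like for like, the drop is from 82.8% to 72–78% (unpooled), or from 80.0% to 68–74% (pooled null variance). The direction is the same either way.

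**The wording suggests an evaluation of two strategies, not of pairs of arms.** The article speaks of evaluating two strategies and of one or both being effective. For main effects the design exceeds 80% comfortably. This stands, and it limits the point: the shortfall belongs to the pairwise comparison behind the stated figure, not to every analysis the design permits.

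**Baseline measurements could recover the loss.** Measurements are planned before and after implementation. Adjustment could raise power, but by how much depends on a before–after cluster correlation that the article does not give. The figures here are therefore before any such adjustment.

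**The plan is provisional.** That makes a correction easy; it does not make the stated power right.

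**A stronger reading to avoid.** A reader might infer that A, B and C will each be tested against D, so that power is only 50–60% after a Bonferroni correction, or that family-wise error reaches 12% (three tests) or 19% (all six pairs). The article states no such set of tests, and the handling of multiplicity may properly sit in an analysis plan that is not shown. Those figures are not part of this point.

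**Conclusion.** The point holds in a limited form. The stated 80% is the normal-approximation power of one arm against one other arm. For that comparison a cluster-level t analysis gives about 71–72% with 8 df and 78% with 16 df, a shortfall of roughly 2 to 9 percentage points from the stated figure.

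This rests on equal allocation, equal cluster sizes, a two-sided 5% test, an intra-cluster correlation of 0.10 and no baseline adjustment. A one-sided test would need only 4.03 clusters per arm by the normal approximation, so sidedness matters. Unequal cluster sizes or a higher correlation would lower power further. That the contrast is pairwise is inferred, but it is the only kind of contrast tried that returns about 80%.

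It does not follow that the trial as a whole is underpowered: main effects would have about 97% (94% at 2.5% each) if the effects are additive and each is 30 points. The article attributes the 30-point gain only to the decision aid, so for the provider strategy that size is an assumption. This is a specific figure to correct and a contrast to name, and not a fatal flaw in the design.

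**What to change.** In the sample-size paragraph:

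1. State that 20 clusters is the trial total, 5 per arm, and state the allocation ratio and sidedness.
2. Name the contrast that the power refers to.
3. Replace the 80% with a t-based cluster-level figure for that contrast: about 72–78% for one pairwise comparison (saying which degrees of freedom are used), or, for the two main effects with 10 against 10 clusters, about 97% at 5% or 94% at 2.5% each, with the additivity and 30-point assumptions written out.
4. If credit is taken for baseline adjustment, state the assumed before–after correlation.

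The cost is a few sentences and no extra clusters. The downside is a less favourable pairwise figure, or, if main effects are chosen, reliance on there being no strong interaction between the strategies. If the sponsor wants to keep 80% for a single unadjusted pairwise comparison, about 6 clusters per arm (24 in all) would give 80–82% with 10 df; that is an option, not a requirement of this point.
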